## Abstract

Restless Legs Syndrome (RLS) is a common sleep disorder characterized by an urge to move the legs that is responsive to movement (particularly during rest), periodic leg movements during sleep, and hyperarousal. Recent evidence suggests that the involvement of the adenosine system may establish a connection between dopamine and glutamate dysfunction in RLS. Transcranial magnetic stimulation (TMS) is a non-invasive electrophysiological technique widely applied to explore brain electrophysiology and neurochemistry under different experimental conditions. In this pilot study protocol, we aim to investigate the effects of dipyridamole (a well-known enhancer of adenosinergic transmission) and caffeine (an adenosine receptor antagonist) on measures of cortical excitation and inhibition in response to TMS in patients with primary RLS. Initially, we will assess cortical excitability using both single- and paired-pulse TMS in patients with RLS. Then, based on the measures obtained, we will explore the effects of dipyridamole and caffeine, in comparison to placebo, on various TMS parameters related to cortical excitation and inhibition. Finally, we will evaluate the psycho-cognitive performance of RLS patients to screen them for cognitive impairment and/or mood-behavioral dysfunction, thus aiming to correlate psycho-cognitive findings with TMS data. Overall, this study protocol will be the first to shed lights on the neurophysiological mechanisms of RLS involving the modulation of the adenosine system, thus potentially providing a foundation for innovative “pharmaco-TMS”-based treatments. The distinctive TMS profile observed in RLS holds indeed the potential utility for both diagnosis and treatment, as well as for patient monitoring. As such, it can be considered a target for both novel pharmacological (i.e., drug) and non-pharmacological (e.g., neuromodulatory), “TMS-guided”, interventions.

## Introduction

Restless Legs Syndrome (RLS) is a common neurological disorder, affecting approximately 5% of people in the USA and Europe, who experience symptoms at least weekly [1]. Typical clinical manifestations include a periodic, rest-induced, predominantly nocturnal urge to move the legs, periodic leg movements during sleep (PLMS), and hyperarousal. Despite the absence of significant complaints of excessive daytime sleepiness, RLS patients exhibit poor total sleep time and quality, which affects also diurnal activity and functioning [2]. The current understanding of RLS pathophysiology involves two distinct yet interrelated neurotransmission systems, namely dopamine (DA) and glutamate (Glu), each primarily associated with the two main clinical features of RLS: PLMS and hyperarousal, respectively. Nevertheless, recent experimental evidence suggests that alterations in adenosine activity may provide a link between these two systems in RLS [3]. Adenosine, a key endogenous sleep-promoting factor, serves indeed as a potent modulator of both DA and Glu neurotransmission [4].

Dipyridamole, a non-selective inhibitor of nucleoside transporters ENT1 and ENT2, increases extracellular adenosine levels. In a recent open-label clinical trial, untreated primary RLS patients receiving dipyridamole demonstrated significant improvement in clinical complaints, PLMS, and total sleep time [5]. Conversely, caffeine, a well-known arousal-promoting psychostimulant, acts as a non-selective adenosine receptor antagonist. Metabolized to paraxanthine and theophylline, caffeine produces arousal effects through partial (25-50%) and non-selective blockade of adenosine receptors [6]. Recently, daily mocha coffee intake was associated with higher cognitive and mood status in non-demented patients with geriatric depression and vascular cognitive impairment, with a significant dose-response association even with moderate consumption [7,8].

In this context, genome-wide association studies have indicated an increased risk of RLS in populations with genomic variants of the protein tyrosine phosphatase D-type cell adhesion molecule receptor (PTPRD). As such, PTPRD, expressed abundantly by DA neurons, may play a crucial role in reconfiguring neural circuits, including interactions between homomeric and heteromeric G-protein-coupled receptors that mediate dopaminergic modulation [9]. Long-term activation of a DA receptor subtype may increase the expression of receptor subtypes with opposing modulatory actions, indicating the significance of dopaminergic interactions at both spinal and supraspinal levels in RLS. These interactions may extend to adenosine A1 and A2A receptors, which are prominent in the striatum, a key structure involved in RLS [10], thus offering new potential pharmacological targets for RLS treatment [9].

While promising, however, the neurophysiological correlates of the neurochemistry underlying RLS remain poorly explored. Transcranial magnetic stimulation (TMS) is a non-invasive neurophysiological technique allowing a “real-time” access to the excitatory and inhibitory electrophysiological properties of cortical and cortico-subcortical neuronal networks *in vivo* [11]. In contemporary research, various protocols are commonly employed to assess brain physiology under diverse experimental conditions, encompassing neuromodulatory interventions [12] and pharmacological manipulations [13]. Within this context, only a limited number of previous studies have indicated that global cortico-motor excitability to TMS appears unaffected by caffeine in healthy subjects [14–16]. However, two more recent papers suggest that a gamma-amino-butyric acid (GABA)-mediated index of cortical inhibition, specifically the cortical silent period (CSP) [17], and a measure of excitation mainly mediated by glutamate, i.e., the intracortical facilitation (ICF) were reduced [18]. Conversely, to the best of our knowledge, no TMS study has been conducted on dipyridamole.

Regarding the application of TMS in sleep, in recent years, several studies have investigated electrocortical patterns in response to TMS in different sleep disorders [19,20], including RLS. These studies are based on evidence demonstrating a circadian-modified excitability of the primary motor cortex (M1), sensory-motor network, and cortico-spinal tract in individuals with RLS [21,22]. Specifically, RLS exhibits a global profile of cortical hyperexcitability, which has been primarily attributed to increased motor cortex excitability and abnormal synaptic plasticity compared to healthy sleepers, although a “disinhibition” (i.e., mainly due to a reduced GABAergic tone) may contribute [22,23]. Notably, this finding appears to be specific to RLS rather than a generic reflection of sleep architecture alterations, thus allowing to draw a relatively specific RLS pattern to TMS, at least in those with a primary disorder and not affected by other sleep problems [19,24]. These findings align with electroencephalography (EEG) evidence of a hyperarousal state at the sleep onset of RLS subjects [25]. This hyperexcitability, partly resulting from electrocortical disinhibition, may also have therapeutic implications and be a potential target for neuromodulatory interventions [12]. Within this framework, a recent study has demonstrated impairment in the GABA circuitry associated with disrupted neuroplasticity in patients compared to controls [23].

Lastly, it is well-established that sleep plays a crucial role in both cognition and mood regulation. However, it remains uncertain whether cognitive impairment in some RLS patients would be solely a consequence of chronic sleep loss and fragmentation or an additional feature of the syndrome [26]. Nonetheless, there is evidence suggesting that RLS patients may exhibit cognitive deficits, particularly in memory, attention, and executive functions [27–29], also in the pediatric age [30,31]. This finding has also been linked to alterations in adenosine neurotransmission, supported by the evidence that adenosine receptors exert a significant role in modulating and adapting various homeostatic brain functions, including cognitive abilities [32,33].

Based on these considerations, a combination of dipyridamole and caffeine in the modulation of adenosine system, in both directions (i.e., up- or down-regulation, respectively), might be apply for a new and “pharmaco-TMS”-based treatment of RLS. Therefore, in this pilot study protocol, we aim to analyze the differential effects of dipyridamole and caffeine, compared to a placebo, on a number of specific measures of cortical excitability to TMS in patients with primary RLS. Initial assessments will include single- and paired-pulse TMS to evaluate cortical excitability. Then, based on the obtained measures, we will investigate the effects of dipyridamole and caffeine on TMS parameters of cortical excitation and inhibition in RLS patients. Lastly, we will assess psycho-cognitive performance in RLS patients to screen them for cognitive impairment and/or mood-behavioral dysfunction, which will eventually allow to correlate psycho-cognitive scores and TMS data.

## Materials and methods

### Study design

The study employs a double-blind, randomized, cross-over exploratory design. Each subject will receive dipyridamole, caffeine, or a placebo in a random sequence determined by computer-generated random numbers. The administration will occur during three different TMS sessions in the late afternoon (in accordance with the circadian distribution of RLS symptoms), with a sufficient wash-out period (at least 2 times the half-life of each substance) between sessions. To enhance the randomness of the sequence, planned restrictions will be unavailable to the contributors enrolling participants or assigning interventions. The allocation sequence will be implemented using sequentially numbered, opaque, sealed envelopes. Blinding of trial participants, outcome assessors, and data analysts will be maintained also after assignment to interventions.

This study (version v.1.0_14/07/2020) received approval from the research Ethics Committee “CE IRCCS Sicilia – Oasi Maria SS.” on October 25, 2016 (Approval ID: 2016/CE-IRCCS-OASI/1). It adheres to SPIRIT (Standard Protocol Items for Randomized Trials) recommendations in a clinical trial protocol and related documents (Fig 1), and it has been registered in a WHO approved registry, i.e., the ISRCTN registry (registration number: ISRCTN11559397). Any protocol amendments or relevant modifications (such as changes to eligibility criteria, outcomes, analyses) will be communicated to relevant parties, including investigators, the research Ethics Committee, trial participants, trial registries, journals, and regulators. The recruitment period for this study will range from March 01, 2024, to February 28, 2025. Written informed consent will be signed by all subjects prior to the inclusion in the study; additional consent provisions for participant data collection and use will be obtained, if necessary. Authorship eligibility of protocol contributors will follow the guidelines of the International Committee of Medical Journal Editors (ICMJE).

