### Assessment

This is a single center, double blind, randomized, 3-period 3-treatment, random-sequence crossover study. After the baseline TMS assessment, the same participants will be orally exposed to all substances (dipyridamole, caffeine, or placebo), in a random order, after a washout period. Participants and researchers involved will be blind to the substance’s nature. More in details, the “dipyridamole arm” will consist of a single oral dose of dipyridamole 75 mg, while the “caffeine arm” of a single oral dose of caffeine 200 mg. After an approximately one-hour interval (the absorption peak of dipyridamole and caffeine is known to occur in about 60 minutes after the oral intake), TMS tests will be repeated to evaluate potential effects of the active compounds compared to placebo. All capsules (active and placebo), prepared by the Pharmacy Department of the Oasi Research Institute-IRCCS, will be indistinguishable. Clinical evaluation and IRLS-RS will be repeated after each experimental condition. Discontinuation or modification of interventions will be allowed, if necessary (e.g., dose change in response to harms or worsening disease), and all the procedures needed to improve adherence to intervention protocols and monitoring will be taken into account. There will be no other relevant or concomitant treatment during the interventions.

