### Statistical analysis

After the analysis of descriptive statistics, based on the results of the Shapiro–Wilk normality test, each outcome will be compared across the three treatment conditions by a repeated-measures ANOVA (if data are normally distributed) or the nonparametric Friedman ANOVA (if data are not distributed normally). After the completion of the data collection, a power analysis will be carried out in order to check if the statistical power of at least 80% is achieved and plan an eventual study extension is needed or not. In any case, the planned number of patients will allow to obtain a power of 80% (with alpha 0.05) even with a “moderate” effect size, as small as 0.465 [44]. No missing data are expected because we plan to continue the recruitment until we reach a number of 30 participants with a complete research protocol.

Fig 2 illustrates the flow chart and main procedures of the study protocol.

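### The two-half-life washout floor allows up to 25% of the previous substance to remain at the next dosing, so the rule does not secure an adequate washout

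*Protocol article*

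**What the plan says.** The Assessment section describes the design: "This is a single center, double blind, randomized, 3-period 3-treatment, random-sequence crossover study". Each patient takes "a single oral dose of dipyridamole 75 mg", "a single oral dose of caffeine 200 mg" and placebo, and TMS is repeated about one hour after intake.

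The Study design section has the only numerical washout rule: "with a sufficient wash-out period (at least 2 times the half-life of each substance) between sessions". On timing it adds: "The administration will occur during three different TMS sessions in the late afternoon". The Assessment section mentions washout again, without a length: "orally exposed to all substances (dipyridamole, caffeine, or placebo), in a random order, after a washout period". The text gives no half-life, no interval in hours or days, and no limit on residual drug.

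Under Statistical analysis, "each outcome will be compared across the three treatment conditions by a repeated-measures ANOVA", with the Friedman test as the non-normal alternative.

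**The concern.** Every comparison in this trial is within patient, so each condition must start free of the one before. The protocol does not leave the washout open: it sets a multiple of the half-life and describes the result as adequate. Two half-lives is a short multiple, and a session can comply fully with the rule while a quarter of the previous substance is still present.

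Three features of this trial make that matter:

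- Residue of either drug enters the placebo session, which is the reference for both drug effects.
- The two drugs are chosen to act on the adenosine system in opposite directions, so residue of one works against the other.
- The Introduction says caffeine is metabolized to paraxanthine and theophylline, but the rule refers only to the substances given.

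A comparison of the three conditions alone would not show a residue effect, so protection has to come from the gap itself.

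**Working it through.** **Inputs.** From the protocol: a minimum of 2 half-lives; doses of 75 mg and 200 mg; late-afternoon sessions; three periods and three treatments; 30 patients; effect size 0.465 with alpha 0.05 and 80% power. Assumed, because the protocol gives no values: half-lives of 5 to 12 hours; first-order elimination; carry-over on the TMS measures proportional to remaining drug.

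**1. Residue under the rule.** The fraction left after k half-lives is 0.5^k. The protocol states no residual fraction, so there is no figure of its own to reproduce here.

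| Half-lives | 2 | 3 | 4 | 5 |
|---|---|---|---|---|
| Residue | 25% | 12.5% | 6.3% | 3.1% |

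At two half-lives the nominal residue is 0.25 × 75 = 18.75 mg dipyridamole or 0.25 × 200 = 50 mg caffeine. This step needs no half-life value.

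**2. Residue at a 24-hour gap.** If the sessions fall on different days, their timing makes about 24 hours the practical minimum. Residue is then 0.5^(24/h) for half-life h.

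| Assumed half-life (h) | 5 | 6 | 8 | 10 | 12 |
|---|---|---|---|---|---|
| Residue at 24 h | 3.6% | 6.3% | 12.5% | 19% | 25% |

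All of these comply with the two-half-life rule; at 12 hours the gap is exactly two half-lives.

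**3. Effect on the drug-placebo differences, balanced orders.** Let the true effects against placebo be d (dipyridamole) and c (caffeine), and let r be the residue carried from the preceding session. Over the six orders, each treatment directly follows each other treatment in 2 of 6. Then:

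- mean under dipyridamole = d + rc/3
- mean under placebo = r(d + c)/3
- difference = d(1 − r/3), and likewise c(1 − r/3) for caffeine

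The retained fraction is 1 − 0.25/3 = 0.917 at 25%, 1 − 0.125/3 = 0.958 at 12.5%, 0.988 at 3.6% and 0.990 at 3.1%. Counting residue from two sessions back subtracts a further r²/6. At 25% that gives 1 − 0.0833 − 0.0104 = 0.906.

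**4. Unbalanced orders.** Here 30 patients were allocated to the six orders without restriction in 20,000 simulations, with d = 1 and c = −1. The central 95% of retained dipyridamole-placebo effects was 0.82 to 1.02 at 25% residue and 0.98 to 1.00 at 3.1%. In about 4% of allocations the retained effect exceeded 1, so the dilution reversed.

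**5. Power, as an illustration.** Read 0.465 as a paired standardized difference (an assumption). With n = 30, a paired t-test reproduces the protocol's 80% only with one-sided alpha 0.05 (0.800). Two-sided it gives 0.69, and the washout figures below start from there.

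| Residue | Retained effect | Two-sided power |
|---|---|---|
| None | 1.000 | 0.69 |
| 3.1% | 0.990 | 0.68 |
| 12.5% | 0.958 | 0.66 |
| 25% | 0.917 | 0.62 |
| 25%, two periods back counted | 0.906 | 0.61 |

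Offsetting a retained fraction of 0.917 takes about 30/0.917² = 35.7, or 36 patients.

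**6. What a longer gap gives.** Five half-lives at 5 to 12 hours is 25 to 60 hours. Next-day sessions at 24 hours just miss this even at 5 hours; a 3-day gap (72 hours) covers half-lives up to 72/5 = 14.4 hours. A 7-day gap covers up to 168/5 = 33.6 hours.

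**The case against.** The rule is a minimum, and the schedule probably forces at least 24 hours. At that gap 25% remains only if the half-life is 12 hours, the top of the assumed range. At 5 hours the residue is 3.6% and the retained effect 0.988, practically the same as under a five-half-life rule. How much is lost in practice therefore depends on half-lives the protocol does not give. That is correct, and it is why 25% is presented as an upper limit.

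Residual drug is also not residual effect. A small remainder may leave the TMS measures unchanged, and nothing in the protocol supports proportional carry-over. This stands as a limit on steps 3 to 5, but not on step 1.

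Other points have some weight. The Study design section refers to planned restrictions on the sequence, so the unrestricted simulation may be too pessimistic. Most of the drop from 80% to 0.62 comes from the two-sided reading, not from the washout. A condensed article need not name a carry-over term, so its absence is not held against the plan. Figures 1 and 2 were not visible in the copy reviewed and might show visit spacing. Finally, patients must be symptomatic and drug-free, so two 7-day gaps would extend the untreated time by about two weeks; a 3-day gap asks for much less.

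None of this rescues the written rule. It sets a specific minimum, and that minimum does not support the description given to it.

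**Conclusion.** The concern holds. The stated minimum permits up to 25% residue at the next dosing, by arithmetic that requires only first-order elimination, and no text in the article sets a longer gap.

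The consequence is moderate. Under proportional carry-over and balanced orders, drug-placebo differences are diluted by up to 8 to 9%. The dilution is about 4% at a mid-range half-life of 8 hours with next-day sessions, and about 1% at 5 hours. Under the paired reading of 0.465, the worst case costs about 7 to 9 points of power (0.69 to 0.62 or 0.61). With unbalanced orders the distortion can be larger or smaller.

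The change is worth making even in an exploratory pilot: the bias falls on the reference condition as well as the active ones, and a slightly longer gap nearly removes it.

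**What to change.** Replace the two-half-life minimum with one of these:

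- at least five half-lives of the longest-lived parent drug or active metabolite, with the half-life values stated; or
- a fixed gap in days. Three days is enough under the assumed 5 to 12 hours. Seven days is the more cautious choice if longer-lived metabolites are a concern.

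Record the actual interval since the previous dose at each session. If the team already intends longer gaps, the text should say so.

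Optional and secondary: balance the six sequences, and add a sensitivity analysis that includes the preceding treatment.

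The cost is one line of protocol wording, one recorded field per session and a few more days between visits. No extra patients or procedures are needed. The price to weigh is the added drug-free time for symptomatic patients, which favours three days over seven if the half-lives allow it.

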**Fig 1 pone.0302829.g001:**
[figure not shown]
SPIRIT schedule. RLS = Restless Legs Syndrome; TMS = transcranial magnetic stimulation.

### Participants

Patients will be recruited from a community clinic at the Department of Neurology IC and Sleep Research Center of the Oasi Research Institute-IRCCS in Troina (Italy), upon their first diagnosis. They must meet all the inclusion criteria and none of the exclusion criteria, whether as out-patients or in-patients. Recruitment and clinical assessment will be supervised by a trained neurologist expert in sleep medicine and disorders ([name]). Given the novelty of the study, sample size calculation relies on similar articles in the literature and the typical sample size in TMS research, indicating a minimum of 30 *de novo*, drug-free, patients. All strategies for achieving participant enrolment to reach target sample size will be adopted, as well as plans to promote participant retention and follow-up completion.

Inclusion criteria will be: i) age 18-65 years; ii) diagnosis of RLS according to the latest criteria by the International RLS Study Group [34]; iii) RLS symptoms on 3 or more days per week for at least 3 months; iv) International RLS Rating Scale (IRLS-RS) score >15 (i.e., moderate symptomatology, at least); v) normal brain magnetic resonance imaging (MRI) and upper limb electromyography (EMG), including the study of the F-waves; vi) women of childbearing potential must have a negative pregnancy test and agree not to become pregnant during the whole experimental procedure; vii) personally signed and dated informed consent obtained before any procedure. All personal information about potential and enrolled participants will be collected and maintained, in order to protect confidentiality before, during, and after the whole procedure.

Exclusion criteria will be: i) drug intake affecting cortical excitability or cognitive performance, including those used for RLS; ii) Mini Mental State Examination score <24; iii) any major psychiatric disease; iv) other neurological or sleep disorders; v) severe, untreated, acute, or not compensated medical illness; vi) any secondary form of RLS (i.e. renal failure, anemia, low serum iron and ferritin levels, pregnancy, peripheral neuropathy, etc.); vii) contraindication to dipyridamole and/or caffeine intake; viii) any condition precluding MRI or TMS execution, such as the presence of a cardiac pacemaker, defibrillator, or mechanical valve, presence of non-compatible joint prostheses, previous neurosurgical procedures, and, for TMS only, seizure or history of epilepsy [35]. A conventional EEG will be also performed to exclude a predisposition to seizure.

